## Introduction

### Slow-release oral morphine as an alternative OAT

Methadone and buprenorphine/naloxone are common pharmacological treatments for opioid use disorder (OUD) aimed at reducing unregulated opioid use, overdose risk, and associated harms.[1–10] However, not all individuals respond well to these treatments, necessitating alternative options such as slow-release oral morphine (SROM), extended-release naltrexone, extended-release buprenorphine, and injectable opioid agonist therapies.[6,8,11] Methadone, a full mu-opioid receptor agonist, has long been the gold standard for OAT due to its high retention rates but requires careful dose titration due to its long half-life, overdose risk, and potential for QT (a measure of the heart’s electrical cycle on electrocardiogram) prolongation.[12] Buprenorphine/naloxone, a partial agonist, has a better safety profile but exhibits a ceiling effect on opioid receptor activation, which may limit its efficacy for individuals with high opioid tolerance.[6]

In contrast, SROM is a full agonist with a long-acting formulation which provides stable plasma levels with once-daily dosing without a ceiling on its opioid effects, making it a potential alternative to methadone and buprenorphine/naloxone. Additionally, unlike methadone, SROM does not prolong the QT interval and may have a lower risk of sedation.[13–15] Originally developed for pain management, SROM has gained recognition as an opioid agonist treatment (OAT) in several countries, including Austria, Germany, and Canada, though its regulatory approval status varies. SROM, marketed as Kadian^®^, a 24-hour extended-release morphine capsule, was introduced in 2017 under British Columbia, Canada’s (BC) provincial drug plan (PharmaCare) as an off-label option for individuals who have not found success with methadone or buprenorphine/naloxone, though it is unclear who are most likely to benefit.[5,6]

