More recently, the pRESTO trial in Vancouver (2021) aimed to evaluate SROM’s effectiveness compared to methadone in fentanyl-exposed populations but was terminated early due to COVID-19, leaving significant gaps in understanding its long-term retention and safety in high-risk patients.[26,27] Observational studies conducted in Germany in 2016 and 2017 showed successful transitions from methadone and buprenorphine to SROM,[28] 60.6% retention at 1 year, reduction in heroin and intravenous drug use, and important improvements in mental and physical health among patients with extensive, but often unsatisfactory prior OAT experience.[29] Additionally, a 2021 hospital-based study in Canada found the ability to offer SROM, in addition to methadone and buprenorphine, resulted in increased rates of OAT initiation among hospitalized patients with OUD, high post-discharge retention, and that patients with chronic pain were more likely to initiate with SROM.[30] However, these studies were limited by small sample sizes[30] and did not compare long-term SROM retention to methadone or buprenorphine.[29,30]

Concerns regarding SROM’s safety have raised questions about its role in OAT. A 2016 epidemiological study in France reported high rates of SROM use by injection, and illegal acquisition, indicating significant risks of misuse and diversion.[31] Also in France, a 2020 population-based cohort study (using data from 2012–2014) found that SROM users had 3.8-fold and 2-fold higher overdose incidence and 9.1-fold and 3.9-fold higher mortality incidence compared to buprenorphine and methadone, respectively, along with increased bacterial infections. However, a relatively small cohort of SROM users had more comorbidities such as mental health and alcohol use disorders but were prescribed benzodiazepines less than methadone or buprenorphine users, indicating less comprehensive care than those receiving these conventional treatments and potential selection bias.[32] Nonetheless, evaluating the real-world effectiveness of SROM as second-line treatment, compared to methadone and buprenorphine/naloxone, among key sub-populations and determining who will benefit most from this form of OAT remains a pressing public health concern amid the ongoing overdose crisis.[22,33]

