### Study population

We will consider ten sub-populations, based on their prior experience with OAT, in the target trial emulations to identify people who achieve better outcomes from SROM compared to methadone and buprenorphine/naloxone. In each case, the study population will include adults (≥18 years) and exclude those who are pregnant or incarcerated at OAT initiation, and individuals with a history of cancer or palliative care. OAT episodes will be defined as continuous treatment with no gaps exceeding four days for methadone and SROM or five days for buprenorphine/naloxone (see Fig. 1 for details).

These thresholds align with BC guidelines recommending re-titration after these durations.[6] Key sub-populations include (i) incident users – no history of OAT dispensation dating back to January 1, 1996, (ii) prevalent new users – no dispensation for ≥5 days of methadone and SROM and ≥6 days for buprenorphine/naloxone, intended to capture repeated treatment attempts. (iii) prevalent new users – a history of methadone dispensation within past year of the index OAT episode. (iv) prevalent new users – a history of buprenorphine/naloxone dispensation within past year of the index OAT episode, (v) prevalent new users – a history of methadone and buprenorphine/naloxone dispensation within past two years of the index OAT episode, (vi) prevalent new users – completed methadone induction within past two year of the index OAT episode. Induction completion is defined as no dose change within at least two consecutive weeks, (vii) prevalent new users – completed buprenorphine/naloxone induction within past two year of the index OAT episode, (viii) prevalent new users – completed methadone and buprenorphine/naloxone induction during past five years of the index OAT episode, (ix) prevalent new users – individuals initiated treatment with buprenorphine/naloxone, (x) prevalent new users – individuals initiated treatment with methadone (see Table 2 for details).

Pregnant and incarcerated individuals will be excluded since pregnancy requires unique clinical management for treatment interruptions,[6] and incarceration involves distinct treatment protocols.[57]

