Follow-up	Intention-to-treat (ITT): from time zero to outcome, death, loss to follow-up, 24 months after time zero, or December 31, 2022, whichever occurs first. Per-protocol (PP): additionally, we will assess adherence weekly and censor follow-up at protocol violation (see Table 3).	Same.
Causal contrasts	ITT for the sub-populations (i) to (viii) and PP for all.	Treatment initiator analysis for the sub-populations (i) to (viii), and PP for all.
Analysis plan	ITT: Hazard ratios will be estimated using Cox PH model. To obtain risk curves and risk differences at 24 months, we will estimate the baseline hazard and combine it with covariate effects to compute cumulative risks. To adjust for potential selection bias due to loss to follow-up, we will use inverse probability weighting (IPW) as a function of baseline and time-varying covariates. PP analysis: same except that individual are censored at non-adherence and uncensored individuals are assigned IPW that are a function of baseline and time-varying variables.	*For the study population (i) to (viii)* Initiator analysis: Marginal structural models with treatment weights from propensity scores models and censoring weights due to loss to follow-up. Weights will be estimated as a function of baseline and time-varying covariates. PP: Same as initiator analysis except potential pre- and post-baseline confounders that are associated with adherence to the treatment strategies will be included in the censoring models. *For the study population (ix) to (x)* Same PP analysis as applied to the study population (i) to (viii), except that individuals’ clone are used with a modified censoring mechanism (see Table 3).

* The optimal SROM doses are determined applying 1:6 MET-to-SROM conversion rate as per BC guidelines.[6]

**Table 2: T2:** Target study populations for comparative effectiveness analysis

Study population	Definition	Rationale
Incident users	(i) No history of OAT dispensation, dating back to January 1, 1996	To evaluate treatment outcomes among individuals initiating OAT for the first time
Prevalent new users	(ii) No dispensation for ≥5 days of methadone and SROM and ≥6 days for buprenorphine/naloxone	To capture repeated OAT attempts after a washout period, reflecting common real-world patterns.

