Prevalent new users with past OAT experience	(iii) A history of methadone dispensation within past year of the index OAT episode	To assess individuals with recent prior experience of specific OAT which may influence current treatment response.
	(iv) A history of buprenorphine/naloxone dispensation within past year of the index OAT episode	
	(v) A history of methadone and buprenorphine/naloxone dispensation in past two years of the index OAT episode	
Prevalent new users who had previously completed OAT induction*	(vi) Completed methadone induction within past two year of the index OAT episode	To assess individuals recently stabilized on methadone and buprenorphine/naloxone, which may influence response to new treatment.
	(vii) Completed buprenorphine/naloxone induction within past two year of the index OAT episode	
	(viii) Completed methadone and buprenorphine/naloxone induction in past five years of the index OAT episode	A history of completing both inductions may reflect complex needs or higher tolerance, informing comparative effectiveness.
Individuals initiated treatment with buprenorphine/naloxone	(ix) Individuals initiated OAT with buprenorphine/naloxone will be included. Switching to SROM within 30 days of initiation will be compared with staying on buprenorphine/naloxone in a two-arm study.	Early switching within buprenorphine/naloxone episode may indicate suboptimal response or poor tolerability.
Individuals initiated treatment with methadone	(x) Individuals initiated OAT with methadone will be included. Switching to SROM within 30 days of initiation will be compared with staying on methadone in a two-arm study.	Early switching within methadone episode likely reflects adverse effects such as sedation, emotional blunting, or QT-related cardiac risk.

* Induction completion is defined as no dose change within at least two consecutive weeks.

**Table 3. T3:** Censoring indication in the primary and secondary analyses for comparing slow-release oral morphine versus methadone and buprenorphine/naloxone.

	OAT discontinuation		All-cause mortality		Overdose-related acute-care visits	
	Initiator	Per protocol	Initiator	Per protocol	Initiator	Per protocol
OAT discontinuation	outcome	outcome				
End of study ^a^	C_1_	C_1_	C_1_	C_1_	C_1_	C_1_
Death	C_2_	C_2_	outcome	outcome	C_2_	C_2_
Loss to follow-up	C_2_	C_2_	C_2_	C_2_	C_2_	C_2_
Deviation from inclusion/exclusion criteria		C_2_		C_2_		C_2_
Deviation from the protocol		C_3_		C_3_		C_3_

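### Sub-populations (iii)–(viii) neither restrict nor split by earlier SROM use, and Table 4 has no prior-OAT covariate, so the SROM arm mixes first use with re-use and past drug experience stays unadjusted

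*Protocol article*

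**What the plan says.** The Study population section says the study will "exclude those who are pregnant or incarcerated at OAT initiation, and individuals with a history of cancer or palliative care". Earlier SROM use is not among these exclusions. The same section defines an episode as "continuous treatment with no gaps exceeding four days for methadone and SROM or five days for buprenorphine/naloxone", so a five-day lapse ends an SROM episode.

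In Table 2, row (i) alone shuts out earlier SROM users: "No history of OAT dispensation, dating back to January 1, 1996". Row (ii) is a washout that names SROM: "No dispensation for ≥5 days of methadone and SROM and ≥6 days for buprenorphine/naloxone". Its stated purpose is to capture repeated attempts. Rows (iii)–(v) require past dispensing of methadone, buprenorphine/naloxone or both. Rows (vi)–(viii) require completed induction on one or both. None of (iii)–(viii) mentions SROM. The rationale for (vi)–(vii) is "To assess individuals recently stabilized on methadone and buprenorphine/naloxone, which may influence response to new treatment".

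The Introduction describes SROM as introduced "as an off-label option for individuals who have not found success with methadone or buprenorphine/naloxone" and gives the need as "evaluating the real-world effectiveness of SROM as second-line treatment, compared to methadone and buprenorphine/naloxone". Under Key measures, exposure in (i)–(viii) is the drug dispensed at initiation.

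**The concern.** A client with the required methadone or buprenorphine/naloxone history who has already used SROM, stopped for five days and restarted it counts as an SROM initiator in (iii)–(viii). A client who tried SROM and left it can enter a comparator arm. The SROM arm is then an unknown blend of first use and re-use, although the clinical question that motivates these rows is SROM as a later option.

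There is also a confounding problem. The Introduction (on adapting guidelines) says that earlier OAT experience often shapes later treatment decisions. Table 2 justifies (iii)–(v) by saying that recent experience of a specific OAT may influence response. By that reasoning, earlier SROM use affects both the choice of SROM and retention, yet SROM is the one study drug whose history is neither restricted nor adjusted for. What is at stake is the reading of the primary discontinuation contrast in six of the ten sub-populations.

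**Working it through.** **Step 1. Does any rule handle earlier SROM use in (iii)–(viii)?**

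- General exclusions: pregnancy, incarceration, cancer, palliative care. No.
- Table 2, rows (iii)–(viii): silent on SROM. No.
- Time zero: the first dispensation. Because Table 2 speaks of an index OAT episode, I read this as the start of that episode, which does not bar earlier SROM.
- Table 4: its OAT-experience block has other opioid dispensing, tobacco treatment, prescriber attachment and funding, urine tests and practice size. It has no prior OAT type, prior retention or prior-episode count. The Covariate selection section takes its confounders from a methadone versus buprenorphine/naloxone study.
- hdPS sensitivity analysis: variables related to exposure are excluded, so past SROM would probably not enter.
- Table 5: washouts of 14, 30 and 90 days. A client restarting SROM after 91 days still enters as an initiator.

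**Step 2. What do the arms then contain?**

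| Row | Methadone arm | Buprenorphine/naloxone arm | SROM arm |
|---|---|---|---|
| (iii), (vi) | all have used methadone | own-drug history open | own-drug history open |
| (iv), (vii) | own-drug history open | all have used it | own-drug history open |
| (v), (viii) | all have used methadone | all have used it | own-drug history open |

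**Step 3. Size of the mixing.** The protocol gives no share of restarters and no difference in their risk, so this is an illustration on assumed values. If a share p of the SROM arm are restarters and their risk differs from that of first-time users by g points, the SROM-arm risk shifts by p × g. With g = 10 points:

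- p = 10%: 0.10 × 10 = 1 point
- p = 30%: 0.30 × 10 = 3 points
- p = 50%: 0.50 × 10 = 5 points

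SROM entered the provincial plan in 2017, so p is likely near zero early in accrual and higher by 2022.

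**Step 4. Direction.** A simulation with no average drug difference. All inputs are assumptions:

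- 200,000 clients with up to six starts each.
- Weekly discontinuation hazard 0.08 × exp(u), where u is a person-by-drug effect with SD 0.5 or 0.8.
- The probability of restarting a drug either ignores earlier retention on it or rises with it.
- Unadjusted Cox hazard ratio (HR), SROM versus methadone, over 104 weeks.

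| Restart rule | (ii), all entries | (iii), all entries | (iii), no prior SROM |
|---|---|---|---|
| Restarting ignores past response | 1.00 | 1.00 | 1.00 |
| Past response drives restarts of all three drugs | 1.00 | about 1.03–1.12 | about 1.06–1.29 |

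If past response drives SROM restarts only, the pooled HR in (ii) is about 0.88–0.98, and entries with no prior SROM give 1.00. The exact ranges depend on how the restart rule is coded; the pattern does not.

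The last column of the table shows why a split alone is not enough. In (iii) every methadone entrant is a methadone restarter. If restarters are selected for having done well on methadone, first-time SROM users look worse with no drug difference at all.

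**The case against.** Several points on the other side stand.

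- Repeated attempts are the declared target of (ii), and its washout names SROM. Calling restarts in (ii) a failed exclusion would be wrong.
- The new-treatment wording belongs to (vi)–(vii) only. It cannot mean a drug never used before, because by definition the methadone arm of (vi) and the buprenorphine/naloxone arm of (vii) have used theirs. It can be read as a new episode.
- The second-line wording is in the Introduction. The Objective defines the initiator effect by the initial dispensation, and that effect is well defined as an average over prior exposure.
- Table 5's longer washouts remove the client who was on SROM last week, though not earlier users in general.
- Fig 1 and the supplementary tables are not shown. Fig 1 is captioned as episode construction, so an eligibility rule there is unlikely but cannot be ruled out.
- A footnote under Table 5 mentions the number of treatment interruptions before time zero. It is not tied to Table 4 or to any weight model.

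A reader might infer that the design tilts retention towards SROM, because restarters are those who tolerated it. The documents do not support that. The tilt appears only if SROM restarts alone follow past response, and nothing in the protocol suggests such an asymmetry. Under the same rule for all three drugs it vanishes in (ii) and reverses in (iii). A reader might also infer that the contrast no longer tests SROM as a new treatment. It is a mixture, and its departure from first use depends on a share of restarters that is not stated.

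None of this supplies a rule or a covariate for earlier SROM use in (iii)–(viii).

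**Conclusion.** The point holds for (iii)–(viii) as an unspecified mixture and an unadjusted confounder. For (ii) it holds only as a missing set of covariates. The textual part rests on Tables 2, 4 and 5 and the Methods text as shown.

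The sign and size of any bias are unknown. Under the assumptions tried, the discontinuation hazard ratio with no true drug difference lay between about 0.88 and 1.12 for pooled entries. These figures show that the bias can go either way; they are not estimates for this cohort. They rest on up to six starts per client, on assumed response variation and on unadjusted analysis. The protocol gives neither the restarter share nor how far restarting follows past response. If restarting ignores past response, the bias in the simulation disappears, and what remains is the question of whose effect is being averaged.

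**What to change.** 1. In Table 2 and the Study population section, pre-specify for (iii)–(viii) a split by any SROM dispensation before time zero (none versus any), applied to all three arms. Report both strata. Draw statements about SROM as a new or second-line option from the 'none' stratum, and only with the adjustment in item 2.
2. In Table 4, for (ii)–(viii), add to the treatment model: prior OAT type (methadone, buprenorphine/naloxone, SROM), duration of the last episode on each drug, time since last use, and number of prior episodes. Give never-used its own category.
3. Leave restarts in (ii), where they are intended.

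Cost: wider intervals within strata and some extra modelling. The variables come from PharmaNet dispensing records already held, and the Study status section says no analysis has begun. No client is dropped, since both strata are reported.
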